Valence:Improvement in the valence of thoughts of the future self (i.e., thoughts becoming more positive) among participants in the treatment condition from pre-to-post intervention.A larger improvement in the valence of thoughts of the future self among participants in the treatment condition versus participants in the control condition from baseline to each measurement point post-intervention.VividnessImprovement in the vividness of thoughts of the future self (i.e., the mental image becoming clearer and more detailed) among participants in the treatment condition from pre-to-post intervention.A larger improvement in the vividness of thoughts of the future self among participants in the treatment condition versus participants in the control condition from baseline to each measurement point post-intervention.RelatednessImprovement in the sense of connection to the future self among participants in the treatment condition from pre-to-post intervention.A larger improvement in the sense of connection to the future self among participants in the treatment condition versus participants in the control condition from baseline to each measurement point post-intervention.Improvement in the sense of similarity to the future self among participants in the treatment condition from pre-to-post intervention.A larger improvement in the sense of similarity to the future self among participants in the treatment condition versus participants in the control condition from baseline to each measurement point post-intervention.
(ii)Improvement in quality of future thoughts—Participants will complete the Prospective Imagery Task (PIT) at the baseline and final assessments [47]. The PIT asks participants to generate a mental image in response to 10 negative future scenarios and 10 positive future scenarios and indicate how vivid each image is on a scale from 1 = no image at all to 5 = very vivid.Improvement in the vividness of future thoughts among participants in the treatment condition from baseline to 3-months post-intervention follow-up.A larger improvement in the vividness of future thoughts among participants in the treatment condition versus participants in the control condition from baseline to 3-months follow-up.

*Demonstrating evidence of improvement in clinical outcomes*

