(i)Improvement in symptoms of depression—Participants will respond to the Beck Depression Inventory—II (BDI-II) at baseline and at the 3-month follow-up session [48]. The BDI-II is the most widely used measure of depressive symptoms and has demonstrated good reliability and validity in clinical and nonclinical German samples [49]. The scale is comprised of 21 items assessing the presence and severity of depressive symptoms. Each item includes 4 response options ranging from no experience of symptoms to severe experience of symptoms; for example, 0 – *I do not feel sad* to 3 – *I am so sad or unhappy that I can’t stand it*. Scores are obtained by summing total items and range from 0 to 63. Total scores from 0 to 13 indicate minimal depression, 14 to 19 mild depression, 20 to 28 moderate depression, and 29 to 63 severe depression.Improvement in reported symptoms of depression among participants in the treatment condition from baseline to 3-months post-intervention follow-up.A larger improvement in reported symptoms of depression among participants in the treatment condition versus participants in the control condition from baseline to 3-months follow-up.(ii)Reduction in frequency and severity of suicidal ideation – Participants will respond to the German language validated Columbia – Suicide Severity Rating Scale adapted for use in Research [50] at baseline, each pre-intervention questionnaire, and the 1-week and 3-month follow-up. Based on responses, participant scores will be categorized as low, moderate, or high risk.Improvement in reported frequency and severity of suicidal ideation among participants in the treatment condition from baseline to each measurement occurring post-intervention (i.e., session 3 pre-intervention, 1-week follow up, 3-month follow up).A larger improvement in reported frequency and severity of suicidal ideation among participants in the treatment condition versus participants in the control condition from baseline to each measurement occurring post-intervention (i.e., session 3 pre-intervention, 1-week follow up, 3-month follow up).(iii)Reduction of negative affect, Improvement in Positive Affect—Participants will respond to the German language validated Positive and Negative Affect Scale (PANAS) at every measurement point [51]. The PANAS is made up of two 10-item scales measuring positive and negative affect. Each item is rated on a scale from 1 = Very Slightly, or Not at all to 5 = Extremely. Scores are obtained by averaging responses to items within the positive and negative subscales.Improvement in affect, i.e., increase in positive affect and decrease in negative affect, among participants in the treatment group from pre-to-post intervention and from baseline to 1-week and 3-month follow-up.A larger improvement in affect among participants in the treatment condition versus participants in the control condition from baseline to each measurement occurring post-intervention.(iv)Improvement in self-efficacy—Participants will respond to the German language validated General Self Efficacy Scale (GSES) at baseline and 3-month follow-up [52]. The scale has 10 items assessing participants’ overall sense of self-efficacy with dealing with difficulties. Items are rated on a scale from 1 = Completely Disagree to 4 = Completely Agree. Scores are obtained by averaging scores across all items.Improvement in self-efficacy among participants in the treatment condition from baseline to 3-month follow-up.A larger improvement in self-efficacy among participants in the treatment condition versus participants in the control condition from baseline to 3-month follow-up.

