#### Secondary objective—establishing a proof of concept for the intervention

Assessment of change in targeted cognitive mechanisms and clinical outcomes will be completed as is outlined in the outcomes section. Due to the modest sample size, these analyses will be completed to pilot the method for a full-scale RCT and to explore trends. The significance of effects will be interpreted and discussed within the context of the statistical limitations of a pilot trial.

Between-group differences for participants in the treatment condition versus the control condition will be assessed using independent-sample *t*-tests. Here, interpretation of Cohen’s *d *will be done using between-group standard deviations. The significance of between-subject changes will also be assessed through calculation of a reliable change index (RCI) [53] and evaluation of confidence intervals for mean differences.

Between-group differences in the targeted cognitive mechanisms and clinical outcomes will additionally be assessed through Latent Growth Curve Modeling (LGCM). This analysis will allow us to evaluate the difference in trajectories of change in cognitive mechanisms and clinical outcomes between the control and treatment conditions. The hypothesized changes in thought processes and subsequent clinical outcomes are expected to continue to grow over time post-intervention, rather than improve wholly and discretely at the point of intervention. The LGCM approach will allow us to observe whether this growth hypothesis is borne out.

For all analyses, age and gender will be included as covariates. Gender is included for the potential biasing effect on reports of depression. Cross-nationally, women endorse depression at highly elevated rates versus men [54]. Age is included for the potential biasing effects on future-oriented thinking. The future is conceived differently at different stages of life. Although variation in stages of life is comparatively low given the already constricted age range (18–24), there are still some meaningful differences in life stage that may impact future perspective when comparing an 18 versus 24-year-old.

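### Latent growth curve modelling is applied to all mechanism and clinical outcomes, but BDI-II, PIT and GSES are measured only twice, so the growth question cannot be answered for these three secondary outcomes

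*Protocol article*

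**What the plan says.** In the Protocol article, the section *Secondary objective—establishing a proof of concept for the intervention* (under *Analyses*) sets the scope of the growth model: "Between-group differences in the targeted cognitive mechanisms and clinical outcomes will additionally be assessed through Latent Growth Curve Modeling (LGCM"). No outcome is excepted, and no special specification is given for outcomes with few occasions. The same section gives the reason for the method. Changes "are expected to continue to grow over time post-intervention, rather than improve wholly and discretely at the point of intervention", and the growth model is said to let the investigators see whether that expectation holds. *Research hypotheses* likewise expects the effect, including that on depressive symptoms, to increase with time.

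The section *Outcomes measures* fixes the occasions:

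- Depression: "Participants will respond to the Beck Depression Inventory—II (BDI-II) at baseline and at the 3-month follow-up session".
- Imagery of future events, listed as a targeted mechanism: "Participants will complete the Prospective Imagery Task (PIT) at the baseline and final assessments".
- Self-efficacy, listed as a clinical outcome: "General Self Efficacy Scale (GSES) at baseline and 3-month follow-up".
- Affect, by contrast: "Positive and Negative Affect Scale (PANAS) at every measurement point".

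Table 1 agrees. The BDI-II, self-efficacy and prospective imagery rows are marked only at baseline and the 3-month follow-up. The C-SSRS row and the future-self and mood row are marked at baseline, t2, t3, 1 week and 3 months.

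**The concern.** Two stated parts of the plan do not fit together: an analysis chosen to show the shape of change, and a schedule that gives three of the outcomes one value before and one value after the intervention. A later analysis plan could choose constraints for the model, but it could not create a third assessment.

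The risk is in the reporting. A growth model result for BDI-II, PIT or GSES would rest on a constraint that the plan does not state, and it could be read as evidence that benefit kept growing. The BDI-II is the only depression outcome measure (the PHQ-9 is used for screening), and depression is in the trial's title. The plan also describes these analyses as a rehearsal for a full-scale trial, so the mismatch between method and schedule could carry over to it.

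**Working it through.** The document gives no figure on this point, so there is none to reproduce. The check counts what the data supply against what the model asks for.

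**Inputs.** Two occasions for BDI-II, PIT and GSES; five for C-SSRS and the future-self scales, and at least five for PANAS (*Outcomes measures*, Table 1). Covariates are age and gender (*Analyses*), plus the arm indicator, so 3. The model is assumed to be the usual linear one, because the document does not specify it.

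**Observed moments.** With T occasions there are T means and T(T+1)/2 variances and covariances.

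- T = 2: 2 + 3 = 5
- T = 3: 3 + 6 = 9
- T = 5: 5 + 15 = 20

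**Parameters.** There are 2 factor means, 2 factor variances, 1 factor covariance, and either 1 residual variance (equal) or T residual variances (free).

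| Occasions | Residuals | Moments | Parameters | df | Rank of Jacobian |
|---|---|---|---|---|---|
| 2 | free | 5 | 7 | −2 | 5 of 7 |
| 2 | equal | 5 | 6 | −1 | 5 of 6 |
| 2 | fixed at zero | 5 | 5 | 0 | 5 of 5 |
| 3 | free | 9 | 8 | +1 | 8 of 8 |
| 5 | free | 20 | 10 | +10 | 10 of 10 |

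**Covariates do not help.** With two occasions, each covariate adds 2 moments and 2 parameters. Three covariates give 5 + 6 = 11 moments against 7 + 6 = 13 parameters (free residuals, rank 11) or 6 + 6 = 12 (equal residuals, rank 11). The deficits stay at −2 and −1.

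**Where the deficit lies.** Write the two occasions as 0 and t, intercept variance a, slope variance b, their covariance c, and residual variances e1 and e2.

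- Var(y1) = a + e1
- Cov(y1, y2) = a + tc
- Var(y2) = a + 2tc + t²b + e2

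That is three equations in a, b, c and one or two residual variances, so four or five unknowns. The means are not affected: mean intercept = m1 and mean slope = (m2 − m1)/t are two equations in two unknowns.

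**Constrained versions.**

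- Residuals fixed at zero: 5 against 5, just identified, with no testable fit. The slope is the individual change score divided by t.
- Random intercept with a fixed slope and equal residuals: 2 means + 1 intercept variance + 1 residual variance = 4 parameters, df = 5 − 4 = +1. The one testable restriction is that the variance is the same on both occasions, which says nothing about shape.

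In both, the arm contrast in mean slope is [(m2 − m1) in treatment − (m2 − m1) in control]/t. That is the difference in mean change, rescaled.

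**Growth against a step.** Suppose the arms differ in change by D at 3 months. A step of D at the intervention that then stays flat implies a baseline-to-3-month difference of D. So does a gradual rise that reaches D only at 3 months. The two outcome means per arm are identical, so no constraint can separate the two histories.

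**The case against.** The strongest reply is that the document names only the method. It does not say that the slope is random or that residual variances are estimated, and the parameter count depends on both. A random-intercept model with a fixed slope is identified with two occasions, and the mean change, on which the between-arm contrast rests, is identified throughout. This stands. A reader might infer that no growth model can be fitted, or that any estimate would be arbitrary. The document does not support that: only the split of variance into intercept, slope and residual is undetermined, and constrained versions run. What the reply does not rescue is the stated purpose, because the constrained versions carry no information on shape.

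A reader might also infer that depression is left without a valid between-arm analysis. It is not. The growth model is an addition to t-tests, Cohen's d, a reliable change index and confidence intervals for mean differences, and *Outcomes measures* defines the BDI-II, PIT and GSES comparisons as change from baseline to 3 months. Nor is depression the main outcome: the primary objective is feasibility and acceptability.

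Finally, the analyses are offered as exploratory and are to be read within the limits of a pilot, and nothing in Table 2 (*Progression criteria*) uses a growth model result. This limits the severity. It does not make the growth statement true for outcomes with a single post-intervention value.

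**Conclusion.** The point holds in a limited form. For BDI-II, PIT and GSES, a standard linear growth model is under-identified by 1 or 2 parameters, with or without covariates, and the versions that can be fitted only restate mean change for the arm contrast. The claim that the method will show whether change continues to grow is therefore false for these three secondary outcomes.

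The shortfall in parameters assumes a linear model with random intercept, random slope and estimated residual variance. The conclusion about growth needs only the schedule in Table 1, whatever the specification. PANAS, the future-self scales and C-SSRS have enough occasions for a linear growth model.

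Severity is moderate: an incorrect statement about three outcomes, one of them the only depression outcome measure, with usable comparisons of change still in place and no progression decision affected.

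**What to change.** In the analysis section for the secondary objective:

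1. Restrict the growth model and the growth hypothesis to outcomes with at least three occasions: PANAS, the future-self scales, and C-SSRS. C-SSRS needs a model suited to its scoring, since the plan sorts it into low, moderate and high risk.
2. For BDI-II, PIT and GSES, compare the arms at 3 months with adjustment for the baseline value, and with age and gender as already planned. Keep the other planned summaries of change.
3. State that no trajectory or growth claim is made for these three outcomes, and align *Research hypotheses* for depressive symptoms with this.

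The cost is a few sentences of wording. No new data, visits or participants are needed.

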### Progression criteria

Decisions regarding whether and how to proceed with testing this intervention on a larger scale are based on the feasibility and acceptability outcomes outlined above. Progression criteria are described in Table 2, following best-practice recommendations for progression criteria reporting [55].

**Table 2 Tab2:** Progression criteria

	Go: proceed with RCT	Amend: proceed with changes	Stop: do not proceed unless changes are possible
Feasibility of participant recruitment Can 60 participants be recruited who meet eligibility criteria (20 per group)?	If ≥ 12 participants can be recruited per month, 60 total	If ≥ 8 participants can be recruited per month, 40 total	If no participants can be recruited per month
Feasibility of participant retention Can ≥ 85% of participants be retained in the study until completion?	≥ 85% (95% CI*: 74–92%) retained through session 4 (1 week follow-up)	≥ 60% retained through session 4 (1 week follow-up)	< 60% retained through session 4 (1 week follow-up)
Intervention implementation Based on qualitative and quantitative data from both participants and experimenter	Delivery of intervention judged strongly feasible	Delivery of intervention judged feasible	Delivery of intervention judged possibly feasible
Feasibility of between-session tasks	≥ 60% participants complete between-session tasks	≥ 40% participants complete between-session tasks	< 40% participants complete between-session tasks
Feasibility of virtual reality medium (embodiment and engagement)	≥ 85% participants report acceptable ratings for avatar embodiment, engagement, and recognition	≥ 60% participants report acceptable ratings for avatar embodiment, engagement, and recognition	< 60% participants report acceptable ratings for avatar embodiment, engagement, and recognition
Acceptability of intervention Based on qualitative and quantitative data from both participants and experimenter	Intervention judged highly acceptable	Intervention judged acceptable	Intervention judged potentially acceptable

*Wilson interval calculated based on a sample of *n *= 60

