Acceptability-Feasibility: Assessment of Intervention (Acceptability of Intervention Measure—AIM; Intervention of Appropriateness Measure—IAM; Feasibility of Intervention Measure—FIM)—The AIM, IAM, and FIM are self-report measures of outcomes associated with implementation success [41]. The scales can be modified to reflect the type of service being implemented. Each scale contains four items which are rated on a response scale of 1 = Completely Disagree to 5 = Completely Agree. Scores are obtained by averaging responses for each measure. No items are reverse coded. Each scale has demonstrated strong validity and reliability [42].

Acceptability: Participant Satisfaction and general feedback—participants will respond to a brief survey assessing their satisfaction with the intervention and eliciting any feedback about the exercises. This survey was developed by the investigators for the purpose of this study.

2.
*Secondary objective measures – Establishing a proof of concept for the intervention*
Demonstrating the intended effect on the targeted cognitive mechanisms.

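### The recruitment progression criterion gives no verdict for rates above zero and below 8 per month, and its Stop threshold is practically out of reach

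*Protocol article*

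**What the plan says.** The section Progression criteria bases the decision on whether and how to move to a larger trial on the feasibility and acceptability outcomes, and Table 2 gives the rules. These outcomes are the primary objective (Study objectives).

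For recruitment, the three cells read:
- Go: "If ≥ 12 participants can be recruited per month, 60 total"
- Amend: "If ≥ 8 participants can be recruited per month, 40 total"
- Stop: "If no participants can be recruited per month"

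The other three numeric rows are retention, between-session tasks and the VR medium. Their Stop cells are below 60%, below 40% and below 60%, each starting exactly where Amend ends.

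The two judgement rows use ordered adjectives. The Stop cell for implementation is "Delivery of intervention judged possibly feasible" and the Stop cell for acceptability is "Intervention judged potentially acceptable". Neither row names a level for an intervention judged infeasible or unacceptable.

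**The concern.** A three-way progression rule should assign every possible result to one category. The recruitment row does not: a wide band of poor results sits between Amend and Stop with no label. That band is where a struggling pilot would land, since a trial that opens and advertises will rarely recruit nobody at all. The sponsor would then have to decide what low recruitment means after seeing it, for a criterion that belongs to the primary objective. Progression criteria are fixed in advance to avoid this.

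The two judgement rows raise a smaller matter of the same kind. The worst judgement has no cell that literally describes it.

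**Working it through.** **1. The plan's own figure.** The only computed figure in Table 2 is the Wilson 95% interval for 85% retention at n = 60, given as 74–92%. With x = 51, p = 0.85 and z = 1.96:
- centre = (p + z²/2n) / (1 + z²/n) = (0.85 + 0.0320) / 1.0640 = 0.829
- half-width = z·√(p(1−p)/n + z²/4n²) / (1 + z²/n) = 1.96 × √(0.002125 + 0.000267) / 1.0640 = 0.090
- interval = 73.9% to 91.9%

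The stated interval is reproduced.

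**2. Implied recruitment window** (totals and rates from Table 2). Go: 60/12 = 5 months. Amend: 40/8 = 5 months. The two cells agree, but the article does not state the window.

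**3. Verdict by rate, using the wording of the row.**

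| Recruited per month | Total over 5 months | Verdict |
|---|---|---|
| 0 | 0 | Stop |
| 1 to 7 | 5 to 35 | none |
| 8 to 11 | 40 to 55 | Amend |
| 12 or more | 60 or more | Go |

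Average rates need not be whole numbers. A total of 39 is 39/5 = 7.8 per month, still below 8, so every total from 1 to 39 is unclassified.

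**4. How often the gap is hit.** Assume Poisson accrual with mean 5r over the window, where r is the true monthly rate. P(Stop) = P(0) = exp(−5r). P(no verdict) = P(1 to 39).

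| r | P(Stop) | P(no verdict) |
|---|---|---|
| 0.5 | 8.2% | 91.8% |
| 1 | 0.7% | 99.3% |
| 2 | 0.005% | >99.9% |
| 5 | <0.001% | 99.7% |
| 6 | <0.001% | 95.4% |
| 7 | <0.001% | 78.0% |

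**5. Comparison with the percentage rows.** These can return Stop. The probabilities below are exact binomial; n = 40 for tasks and VR ratings is an assumption, taken from the number planned to receive the intervention (Sample size).
- Retention, n = 60, Stop at 35 or fewer: 92% if the true rate is 50%, 99.9% if it is 40%.
- Between-session tasks, n = 40, Stop at 15 or fewer: 88% if the true rate is 30%.
- VR ratings, n = 40, Stop at 23 or fewer: 87% if the true rate is 50%.

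**The case against.** The strongest reply is that the gap does little harm. A rate of 1 to 7 per month fails both cells that allow the trial to go forward, so nothing in Table 2 licenses proceeding. That is right, and a reader should not infer that near-failed recruitment would be waved through. It does not supply a verdict, however. The table still does not say whether such a result means Stop or something milder, and it places the stated Stop at zero.

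The Stop cell might also be read as one month with no recruits. The parallel wording of Go and Amend points to an overall rate. Even on the other reading, a steady rate of 1 to 7 with no empty month has no verdict.

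A reader might be tempted by several stronger readings, and the document does not support them.
- *The progression rule as a whole cannot return Stop.* Three of the six rows have complete cuts and return Stop readily at plausible bad values.
- *Implementation and acceptability have no failing category.* Both have a filled Stop cell, the levels are ordered, and anything short of feasible or acceptable already falls there. A worse judgement would reasonably be read as Stop too. The fault is in the label.
- *Low recruitment matters because fewer than 30 would receive VR,* the number that Sample size calls sufficient for the intervention arm. At 7 per month the figure is 35 × 2/3 = 23.3, but at 8 per month it is 40 × 2/3 = 26.7, also below 30. The comparison does not separate the unclassified band from Amend.
- *The adjectives have no score cut-offs.* The acceptability, appropriateness and feasibility scales are specified ("Each scale contains four items which are rated on a response scale of 1 = Completely Disagree to 5 = Completely Agree"), and how their scores map to the adjectives is detail that an article may leave to the full protocol or analysis plan. Drawing also on qualitative data and the experimenter's view is a legitimate choice in a pilot.

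**Conclusion.** The point stands for the recruitment row. Rates above 0 and below 8 per month are unclassified whatever the window; the translation to totals of 1 to 39 rests on the inferred 5 months. That Stop is practically unreachable rests on the Poisson assumption and on reading the cell as zero recruitment overall. On that basis its chance is below 1% at any true rate of 1 per month or more. This is a threshold that the article states and sets badly, out of line with the other numeric rows of the same table, and nothing elsewhere in the article closes the gap.

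For implementation and acceptability only a wording point remains. The defect touches the progression decision alone. Randomisation, data collection and effect estimates are unaffected, and progression is not the pilot's only purpose, since proof of concept is a key secondary objective.

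**What to change.** Change the recruitment Stop cell to *fewer than 8 per month (fewer than 40 in total)*. This uses the sponsor's own Amend boundary and matches the form of the percentage rows. Another cut is acceptable if Amend is moved to meet it, so that no rate is left without a verdict. It would help to state the 5-month window if that is what is meant.

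Reword the two judgement Stop cells so that they extend downwards, for example *at most possibly feasible, including not feasible* and *at most potentially acceptable, including not acceptable*.

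This changes three cells and no data collection. The small downside is less freedom to classify low recruitment after the fact. The change should be made before the results are classified.
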